5.4.2 Handling of Participant Withdrawals or termination

The participants who withdraw or discontinue early will not be replaced.

## 5.5 Premature Termination or Suspension of Study

April 2014

# 6 STUDY AGENT

## 6.1 Study Agent(s) and Control Description

**Diet Intervention**

Both diets are aimed for a moderate, long-term, weight loss with restricted intake of *trans*-fats and refined carbohydrates, and increased intake of vegetables. Lunch, typically the main meal in this population, will be provided exclusively by the workplace cafeteria. A dietitian will be working closely with the kitchen staff to adjust the diets to the specific diet groups. The 18-month dietary intervention will include 90-minute nutritional session in the workplace with clinical dietitians every week during the first month of the intervention, and every month thereafter. Participants will be instructed to adhere to their specific diets during the entire week. To ensure that the intensity of treatment was equal between the two dietary intervention groups, the workshop format and the quality of the materials delivered during these sessions will be similar across the diet groups.

For the LF diet, the aim is to limit total fat intake to 30% of calories, with up to 10% of saturated fat, and no more than 300 mg of cholesterol per day, and to increase dietary fiber. Participants will be counseled to consume whole grains, vegetables, fruits, and legumes and to limit their consumption of additional fats, sweets, and high-fat snacks.

The MED/LC diet will combine the Mediterranean and low-carbohydrate diets described in our previous weight loss trial (the DIRECT trial^22^). The diet restricted carbohydrate intake to less than 40 g/day in the first two months (induction phase), and thereafter a gradual increase up to 70 g/day, and increased protein and fat intake, according to the MED diet. The MED/LC diet will be rich in vegetables and legumes and low in red meat, with poultry and fish replacing beef and lamb. This group will be also provided 28 g of walnuts/day [160 Kcal/84% fat, mostly PUFA (omega-3 α-linolenic acid)] starting from the third month, after the very low carbohydrate diet during the first two months.

**Physical Activity Intervention**

Starting after the first 6 months of dietary intervention, participants who will be randomized to added PA will receive a free supervised gym membership for the following 12 months. The intervention will include monthly 60-minute educational workshops, and training group sessions at the gym, directed by a certified fitness instructor, who will be blinded to the assigned diets of the participants. The exercise program will include three sessions/week of mostly aerobic training. In the first month participants will start with low intensity of aerobic training at 65% maximum heart rate for 20 minutes and 10 minutes of resistance training. Exercise will gradually increase to 45 minutes of aerobic training at 80% of maximum heart rate and 15 minutes of resistance training. The resistance training will be increased from one set of weights with 60% of the maximum weight up to two sets with 80% of the maximum weight and will include: leg extension, leg curl, elbow flexion, triceps extension, lateral pull-down, lower back extension and bent leg sit-ups.

### 6.1.1 Acquisition

NA

### 6.1.2 Formulation, Appearance, Packaging, and Labeling

NA

### 6.1.3 Product Storage and Stability

NA

### 6.1.4 Preparation

NA

### 6.1.5 Dosing and Administration

NA

### 6.1.6 Route of Administration

NA

### 6.1.7 Starting Dose and Dose Escalation Schedule

NA

### 6.1.8 Dose Adjustments/Modifications/Delays

NA

### 6.1.9 Duration of Therapy

18-month intervention

### 6.1.10 Tracking of Dose

NA

### 6.1.11 Device Specific Considerations

NA

## 6.2 Study agent Accountability Procedures

# 7 STUDY PROCEDURES AND SCHEDULE

## 7.1 Study Procedures/Evaluations

### 7.1.1 Study specific procedures

**Magnetic Resonance Imaging (MRI)**

To assess body fat depots/deposits, we will perform a 45-minute 1.5-Tesla MRI (Ingenia 3.0 T, Philips Healthcare, Best, the Netherlands) scans at baseline and after 18 months. In a sub-set of, randomly selected, 50% of the participants, we will perform MRI measurement after 6 months of intervention. The scanner utilize a 3D modified DIXON (mDIXON) imaging technique without gaps (2mm thickness and 2mm of spacing), fast-low-angle shot (FLASH) sequence with a multi-echo two-excitation pulse sequence for phase-sensitive encoding of fat and water signals (TR,3.6ms; TE1,1.19ms; TE2,2.3ms; FOV 520×440×80mm; 2×1.4×1mm voxel size). Four images of the phantoms will be generated, including in-phase, out-phase, fat and water phase. A breath-hold technique will be used to avoid motion artifacts when the chest and abdomen will be scanned. In all simultaneous fat depots quantifications and comparisons, observers will be blinded to time point and group treatment. All fat depots will be assessed by one or two raters. To validate our mDIXON quantification of fat ratio, we will test five tubes filled with 0%, 25%, 50%, 75% and 100% of oil to observe a linear relation.

***Abdominal fat depots:*** We will quantify abdominal fat using the MATLAB-based semi-automatic software. We will calculate mean VAT and SAT from three axial slices: L5-S1, L4-L5 and L2-L3. Quantification of the fat mass regions will include the area of each fat type and its proportion (percentage) of the total area of all fat types.

***Hepatic fat content:*** We will quantify the percentage of hepatic fat using PRIDE software from Philips Medical Systems. We will calculate mean percentage from four 2D slices (3cm intervals divided into quarters) by utilizing the region of interest (ROI) approach, which is based on measurements of tissue densities (fat/fat+water) using the Fat Ratio Calculation.

***Resting metabolic Rate (RMR)*** We will mesure RMR by indirect calorimetry (QUARK REE by COSMED, Rome, Italy) in which the quantity of oxygen consumed and carbon dioxide produced are measured and converted into kcal using the Weir equation.

**Clinical measurements**

Height will be measured at baseline, to the nearest millimeter by using a standard wall-mounted stadiometer. WC will be measured at baseline, after 6 months (prior to the second randomization), and at 18 months, to the nearest millimeter with an anthropometric measuring tape; the measurement will be made half-way between the last rib and the iliac crest. Body weight will be measured monthly without shoes to the nearest 0.1kg. Fasting blood samples will be taken at baseline and at 18 months, at 8:00am, and will be stored at ‑80°C. Fasting plasma glucose (FPG) will be measured by Roche GLUC 3 (hexokinase method). Plasma insulin will be measured with an enzyme immunometric assay [Immulite automated analyzer, Diagnostic Products, coefficient of variation (CV)=2.5%]. Serum total cholesterol (CV=1.3%), high-density-lipoprotein cholesterol (HDL-c), low-density-lipoprotein (LDL) cholesterol, and triglycerides (CV=2.1%) will be determined enzymatically with a Cobas 6000 automatic analyzer (Roche). Plasma leptin levels will be assessed by ELISA (Mediagnost, CV=2.4%). All biochemical analyses will be performed at the laboratories of the University of Leipzig, Germany.

Changes in resting metabolic rate (RMR) will be performed, using a handheld indirect calorimeter^52^.

### 7.1.2 Standard of care study procedures

NA

## 7.2 Laboratory Procedures/Evaluations

NA

### 7.2.1 Clinical Laboratory Evaluations

### 7.2.2 Other Assays or Procedures

### 7.2.3 Specimen Preparation, Handling, and Storage

### 7.2.4 Specimen Shipment

All the samples will be transported with appropriate bio-material shipping.

## 7.3 Study Schedule

### 7.3.1 Screening

Please refer to Section 7.3.7, Schedule of Events.

### 7.3.2 Enrollment/Baseline

Please refer to Section 7.3.7, Schedule of Events.

### 7.3.3 Follow-up

Please refer to Section 7.3.7, Schedule of Events.

### 7.3.4 Final Study Visit

Please refer to Section 7.3.7, Schedule of Events.

### 7.3.5 Early Termination Visit

NA

### 7.3.6 UNSCHEDULED VISIT

NA

### 7.3.7 Schedule of Events Table

**Table 3: Design of the intervention; the CENTRAL study**

| Year | 2012 | | | | 2013 | | | | | | | | | | | | 2014 | | |
| --- | --- | --- | --- | --- | --- | --- | --- | --- | --- | --- | --- | --- | --- | --- | --- | --- | --- | --- | --- |
| Month of intervention  Event | 0 | 1 | 2 | 3 | 4 | 5 | 6 | 7 | 8 | 9 | 10 | 11 | 12 | 13 | 14 | 15 | 16 | 17 | 18 |
| Dietary sessions |  | ++ | + | + | + | + | + | + | + | + | + | + | + | + | + | + | + | + | + |
| Physical activity intervention – gym membership provided |  |  |  |  |  |  |  | ++ | + | + | + | + | + | + | + | + | + | + | + |
| Whole body MRI | + |  |  |  |  |  | + |  |  |  |  |  |  |  |  |  |  |  | + |
| REE – Indirect calorimetry | + |  |  |  |  |  | + |  |  |  |  |  |  |  |  |  |  |  | + |
| Blood draw and urine samples (fasting) | + |  |  |  |  |  | + |  |  |  |  |  |  |  |  |  |  |  | + |
| Anthropometric measurements (WC, BP) | + |  |  |  |  |  | + |  |  |  |  |  |  |  |  |  |  |  | + |
| Weight measurement | + | + | + | + | + | + | + | + | + | + | + | + | + | + | + | + | + | + | + |
| Electronic questionnaires (FFQ, medical, symptoms, life-style, PA) | + |  |  |  |  |  | + |  |  |  |  |  |  |  |  |  |  |  | + |
| Physician follow-up (including reporting updates in drug usage, safety) |  |  |  |  |  |  | + |  |  |  |  |  | + |  |  |  |  |  | + |

## 7.4 Justification for Sensitive Procedures

NA

## 7.5 Concomitant Medications, Treatments, and Procedures

The medical clinic of the workplace will continue with the routine screening test and treatment

### 7.5.1 Precautionary Medications, Treatments, and Procedures

## 7.6 Prohibited Medications, Treatments, and Procedures

The medical clinic of the workplace will continue with the routine screening test and treatment

## 7.7 Prophylactic Medications, Treatments, and Procedures

The medical clinic of the workplace will continue with the routine screening test and treatment

## 7.8 Rescue Medications, Treatments, and Procedures

The medical clinic of the workplace will continue with the routine screening test and treatment

## 7.9 Participant Access to Study Agent At Study Closure

Participants will be able to be in contact with all investigators during the study and after the study will be complete

# 8 ASSESSMENT OF SAFETY

## 8.1 Specification of Safety Parameters

### 8.1.1 Definition of Adverse Events (AE)

Adverse event means any untoward medical occurrence associated with the use of an intervention in
humans, whether or not considered intervention-related (21 CFR 312.32 (a)).

### 8.1.2 Definition of Serious Adverse Events (SAE)

Serious adverse event or serious suspected adverse reaction. An AE or suspected adverse reaction is
considered "serious" if, in the view of either the investigator or sponsor, it results in any of the following
outcomes: death, a life-threatening adverse event, inpatient hospitalization or prolongation of existing
hospitalization, a persistent or significant incapacity or substantial disruption of the ability to conduct
normal life functions, or a congenital anomaly/birth defect. Important medical events that may not
result in death, be life-threatening, or require hospitalization may be considered serious when, based
upon appropriate medical judgment, they may jeopardize the patient or subject and may require
medical or surgical intervention to prevent one of the outcomes listed in this definition.

### 8.1.3 Definition of Unanticipated Problems (UP)

OHRP considers unanticipated problems involving risks to participants or others to include, in general,
any incident, experience, or outcome that meets **all** of the following criteria:
• Unexpected in terms of nature, severity, or frequency given (a) the research procedures that are
described in the protocol-related documents, such as the IRB-approved research protocol and
informed consent document; and (b) the characteristics of the participant population being
studied;
• Related or possibly related to participation in the research (“possibly related” means there is a
reasonable possibility that the incident, experience, or outcome may have been caused by the
procedures involved in the research); and
• Suggests that the research places participants or others at a greater risk of harm (including
physical, psychological, economic, or social harm) than was previously known or recognized.
This study will use the OHRP definition of UP.

## 8.2 Classification of an Adverse Event

### 8.2.1 Severity of Event

The following guidelines will be used to describe severity:
• **Mild** – Events require minimal or no treatment and do not interfere with the participant’s daily
activities.
• **Moderate** – Events result in a low level of inconvenience or concern with the therapeutic
measures. Moderate events may cause some interference with functioning.
• **Severe** – Events interrupt a participant’s usual daily activity and may require systemic drug
therapy or other treatment. Severe events are usually potentially life-threatening or
incapacitating.

### 8.2.2 Relationship to Study Agent

For all collected AEs, the clinician who examines and evaluates the participant will determine the AE’s
causality based on temporal relationship and his/her clinical judgment. The degree of certainty about
causality will be graded using the categories below.
• **Definitely Related** – There is clear evidence to suggest a causal relationship, and other possible
contributing factors can be ruled out. The clinical event, including an abnormal laboratory test
result, occurs in a plausible time relationship to drug administration and cannot be explained by
concurrent disease or other drugs or chemicals. The response to withdrawal of the drug
(dechallenge) should be clinically plausible. The event must be pharmacologically or
phenomenologically definitive, with use of a satisfactory rechallenge procedure if necessary.
• **Probably Related** – There is evidence to suggest a causal relationship, and the influence of other
factors is unlikely. The clinical event, including an abnormal laboratory test result, occurs within
a reasonable time after administration of the drug, is unlikely to be attributed to concurrent
disease or other drugs or chemicals, and follows a clinically reasonable response on withdrawal
(dechallenge). Rechallenge information is not required to fulfill this definition.
• **Possibly Related** – There is some evidence to suggest a causal relationship (e.g., the event
occurred within a reasonable time after administration of the trial medication). However, other
factors may have contributed to the event (e.g., the participant’s clinical condition, other
concomitant events). Although an AE may rate only as “possibly related” soon after discovery, it
can be flagged as requiring more information and later be upgraded to “probably related” or
“definitely related,” as appropriate.
• **Unlikely to be related** – A clinical event, including an abnormal laboratory test result, whose
temporal relationship to drug administration makes a causal relationship improbable (e.g., the
event did not occur within a reasonable time after administration of the trial medication) and in
which other drugs or chemicals or underlying disease provides plausible explanations (e.g., the
participant’s clinical condition, other concomitant treatments).
• **Not Related** – The AE is completely independent of study drug administration, and/or evidence
exists that the event is definitely related to another etiology. There must be an alternative,
definitive etiology documented by the clinician.] <Insert text>

### 8.2.3 Expectedness

NA

## 8.3 Time Period and Frequency for Event Assessment and Follow-Up

The occurrence of an AE or SAE may come to the attention of study personnel during study visits and
interviews of a study participant presenting for medical care, or upon review by a study monitor.
All AEs including local and systemic reactions not meeting the criteria for SAEs will be captured on the
appropriate CRF. Information to be collected includes event description, time of onset, clinician’s
assessment of severity, relationship to study product (assessed only by those with the training and
authority to make a diagnosis), and time of resolution/stabilization of the event. All AEs occurring while
on study must be documented appropriately regardless of relationship. All AEs will be followed to
adequate resolution.
Any medical condition that is present at the time that the participant is screened will be considered as
baseline and not reported as an AE. However, if the study participant’s condition deteriorates at any
time during the study, it will be recorded as an AE.
Changes in the severity of an AE will be documented to allow an assessment of the duration of the event
at each level of severity to be performed. AEs characterized as intermittent require documentation of
onset and duration of each episode.
The PI will record all reportable events with start dates occurring any time after informed consent is
obtained until 7 (for non-serious AEs) or 30 days (for SAEs) after the last day of study participation. At
each study visit, the investigator will inquire about the occurrence of AE/SAEs since the last visit. Events
will be followed for outcome information until resolution or stabilization.

## 8.4 Reporting Procedures

### 8.4.1 Adverse Event Reporting

Notifications regarding AEs will receive [name], MD, Soroka Medical Center (PI) and [name], MD, Nuclear Research Center-Negev (the head of the integral medical center in Nuclear Research Center).

### 8.4.2 Serious Adverse Event Reporting

### 8.4.3 Unanticipated Problem Reporting

NA

### 8.4.4 Events of Special Interest

### 8.4.5 Reporting of Pregnancy

Women participants will be required to report their pregnancy to [name], MD, Nuclear Research Center-Negev (the head of the integral medical center in the workplace) and the intervention will be discontinued.

## 8.5 Study Halting Rules

NA

## 8.6 Safety Oversight

# 9 CLINICAL MONITORING

The medical clinic of the workplace will continue with the routine screening test and treatment

# 10 STATISTICAL CONSIDERATIONS

## 10.1 Statistical and Analytical Plans

The overall primary outcome is the change in body fat distribution, and the main specific endpoint is VAT, with a priori hypothesis that VAT, specifically, could be differentially and significantly altered by lifestyle intervention strategies. Secondary outcomes will be abdominal subcutaneous fat sub-depot and hepatic fat.

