# PROTOCOL SUMMARY

| **Title:** | **Differential effect of weight-loss diet strategies on dynamics of abdominal and other fat depots and metabolic risk – the CENTRAL study: intervention trial** |
| --- | --- |
| **Précis:** | **Methods**: an estimate of 250 participants who have either a. central obesity or b. lean participants with poor dietary habits combined with hyper TG will be randomized by median VAT to the following groups: **Group 1:** low-fat diet. **Group 2 :** Low-carb /Mediterranean high MUFA and PUFA diet diet. Specific food items will be provided. After 6 months of intervention, the diet groups 1 and 2 will be re-randomized to continue with diet only or with combination of 4 hours/week aerobic and resistance gym exercise for the subsequent year, divided by 4 equal size groups of **Group A** (low-fat diet only), **Group A+** (low-fat diet +physical activity) , **Group B** (Low-carb/ high MUFA & PUFA diet only) and **Group B+** (Low-carb/ high MUFA & PUFA diet + physical activity). All groups will be guided for their dietary intervention by nutritional sessions. All the participants will be followed by 1.5-Tesla MRI imaging of fat and muscle, blood and urine biomarkers, clinical measurements (weight, waist circumference, blood pressure, energy expenditure) and electronic questionnaire of dietary, lifestyle and medical information. Furthermore, genetic tests will be performed following a genetic ethical committee approval. |
| **Objectives:** | To assess whether distinct lifestyle strategies can differentially affect specific body adipose pools.  ***Objective 1:***  To compare the effects of: low-carb/high-MUFA; and the currently recommended diet by the American Heart Association (low-fat diet) on the dynamics of body fat compesition (mainly VAT) during weight loss and regain-plateau phases by MRI with and without physical activity. ***Objective 2:***  To assess the effect of Low-carb/MED and Low- fat diets with or without PA on the dynamics of abdominal suncotenius intra-hepatic fat among participants with abdominal obesity or dyslipidemia. |
| **Endpoint** | Primary Endpoint: Body fat composition (changes in VAT). Important Secondary Endpoints: changes in abdominal subcutaneous fat sub-depots and hepatic fat. |
| **Population:** | Healthy adults with abdominal obesity/dyslipidemia. |
| **Phase:** | Phase 3 |
| **Number of Sites enrolling participants:** | Nuclear Research Center-Negev, Dimona, Israel  250 participants |

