
## 2.2 Rationale

Although accumulation of intra-abdominal fat may be pathogenic, it is unknown whether different diets improve metabolic state through differential effects on intra-abdominal versus subcutaneous-abdominal adipose tissue. While inducing similar global weight loss, low-carbohydrate/Mediterranean (LC/MED) diet strategy more favorably affects "pathogenic" abdominal fat depots when compared to the conventional low-fat diet (LF). These nutritional strategies initiated on top of exercise may manifest by differences in the maximal extent and/or dynamics of decrease in the mass of abdominal fat depots, and correspond to improvement in metabolic risk markers. For this, we propose an 18-month dietary and exercise intervention randomized controlled trial (the CENTRAL study). We hypothesize that differential dynamics in various fat depots: as SAT and VAT in response to two opposing dietary strategies mediate the beneficial metabolic effects during weight loss and regain phases.

Significance – The results of the present study will enhance current understanding on the mechanistic role of different abdominal fat depots (mainly VAT) in the pathogenesis of obesity. Particularly, it will increase current resolution in linking *dynamic* alterations in abdominal fat depots with various components of obesity-related metabolic dys-regulation. From a nutritional point of view, it will unravel the potential differential effect of macronutrients (carbs versus fat) in driving central adiposity. As for public health, the results will shed light on effective, health-promoting lifestyle intervention strategies, and whether they can be tailored individually based on abdominal fat distribution at baseline. This would be achieved by means of addressing the major limitations of currently available studies in the literature, by utilizing long-term intervention study with an expected high adherence rates.

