## 10.2 Statistical Hypotheses

We hypothesize that differential dynamics in various fat depots: as SAT and VAT in response to two opposing dietary strategies mediate the beneficial metabolic effects during weight loss and regain phases.

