## 10.4 Description of Statistical Methods

### 10.4.1 General Approach

Results will be presented as means ± SD unless otherwise stated. Analysis of variance with a covariance (ANCOVA) test will be used in order to assess adherence to the interventions (attendance of the group sessions) and differences in changes nutrient intakes between the diet strategies. General linear models will be used to compare the trajectories of body weight and WC across the four intervention groups. We will use multivariate two-way ANCOVA and compare type of diet and physical activity as fixed factors (2*2 factorial design) to test changes in specific fat depots, using mean of differences and 95% CIs for each intervention group over time. Optional interactions between diet and exercise will be assessed by the ANCOVA models. To assess the effect of the combination of diet and PA, general linear models will be used with LFPA– as the reference. All models will be adjusted for age, sex, baseline abdominal obesity and 18-month weight change. Changes in the various fat depots and deposits will be evaluated both as absolute and relative changes. The association between changes in abdominal fat and intra-hepatic fat, and changes in levels of blood biomarkers will be tested using multivariate linear regression models, adjusted for age, sex, weight change, intervention group and baseline abdominal fat status (for the abdominal fat models) or baseline intra-hepatic fat (for the hepatic model). Homeostasis-model-assessment-of insulin-resistance (HOMA-IR) will be calculated according to the following equation: insulin (U/ml)×fasting glucose(mmol/liter) ÷22.5. Statistical analysis will be performed with IBM SPSS (version 23). All *P*-values will be two-sided, and *P*<0.05 will be considered statistically significant.

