### 10.4.3 Analysis of the Secondary Endpoint(s)

Secondary outcomes will be abdominal subcutaneous fat sub-depot and hepatic fat.

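### The protocol asks whether the diets affect visceral fat differently from subcutaneous fat, but plans no contrast between the two depots

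*Protocol*

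**What the plan says.** **The question.** The Protocol Summary gives the overall aim as "To assess whether distinct lifestyle strategies can differentially affect specific body adipose pools". The Rationale (2.2) says it is unknown whether diets improve metabolic state through "differential effects on intra-abdominal versus subcutaneous-abdominal adipose tissue". The Statistical Hypotheses (10.2) refer to "differential dynamics in various fat depots: as SAT and VAT in response to two opposing dietary strategies", as mediators of metabolic benefit. Sections 10.1 and 10.4.2 name body fat distribution as the overall primary outcome and VAT as the main specific endpoint, "with a priori hypothesis that VAT, specifically, could be differentially and significantly altered by lifestyle intervention strategies".

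**The analysis.** Section 10.4.1 plans a multivariate two-way ANCOVA to "compare type of diet and physical activity as fixed factors (2*2 factorial design) to test changes in specific fat depots". The one interaction it names is between the two randomised factors: "Optional interactions between diet and exercise will be assessed by the ANCOVA models". All models adjust for age, sex, baseline abdominal obesity and 18-month weight change. Changes are to be evaluated on both absolute and relative scales, and every P-value is two-sided at 0.05. The other depots have their own place in the hierarchy: "Secondary outcomes will be abdominal subcutaneous fat sub-depot and hepatic fat" (10.4.3).

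**The measurement.** Under Magnetic Resonance Imaging (7.1.1), quantification covers "the area of each fat type and its proportion (percentage) of the total area of all fat types". No endpoint or test uses those proportions.

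**The concern.** A statement that a diet acts differently on VAT than on SAT is about the difference between two diet effects. Testing each depot for a diet effect does not test that difference. One P-value can fall below 0.05 and the other above it when the true effects are equal, and both can fall below 0.05 when the effects differ.

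The trial could therefore end with a clear answer on VAT and no planned analysis for the question posed in 2.2 and 10.2. Any conclusion that a diet mobilises visceral fat preferentially would then have to be inferred from the pattern of separate results, with no control over how often that inference is wrong.

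**Working it through.** **1. The plan's own figure.** Section 10.5 gives a VAT difference of 3.57 cm², alpha 5%, power 80% and 250 participants, but no SD. The 250 cannot be reproduced forwards, only solved back. For 125 per diet:

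SD = 3.57 × √(125/2) / (1.960 + 0.842) = 28.22 / 2.802 = 10.07 cm².

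This sizing concerns VAT alone. The protocol gives no SD for SAT and no correlation between depots, so everything below rests on assumed values shown as ranges.

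**2. Question against model.**

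| Planned element (10.4.1 or 7.1.1) | What it tests | Is it a VAT-versus-SAT contrast? |
|---|---|---|
| Diet and PA as fixed factors | Arm differences in a depot's change | No; depot is not a factor |
| Diet-by-exercise interaction (optional) | Whether the diet effect depends on PA | No |
| Multivariate ANCOVA, if read as a joint model | Whether any depot differs between arms | No; the joint test does not say which depot, or by how much more |
| Adjustment for weight change | Effect on a depot beyond weight loss | No; it does not ask for more than in SAT |
| Relative change | Each depot on its own proportional scale | No; a common scale, but no comparison on it |
| Depot share of total fat area | Nothing; it is only measured | It could be one, but no test uses it |

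**3. How often separate tests disagree when the effects are the same.** Let the two depot test statistics be bivariate normal with equal means and correlation ρ. The mean is 1.960 + 0.842 = 2.802 for 80% power and 1.960 for 50% power. Compute P(|Z_VAT| > 1.96 and |Z_SAT| ≤ 1.96):

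| ρ | 80% power per depot | 50% power per depot |
|---|---|---|
| 0.3 | 13.4% | 20.2% |
| 0.5 | 11.3% | 16.7% |
| 0.7 | 8.7% | 12.7% |
| 0.85 | 6.1% | 8.8% |

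By symmetry, exactly one of the two depots is significant in twice these proportions: 12-27% at 80% power and 18-40% at 50%.

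**4. What a direct contrast does.** Divide Z_VAT − Z_SAT by √(2 − 2ρ). If the standardised effects are equal, this rejects in 5% of trials, 2.5% in the VAT direction. If the diet acts on VAT only, with 80% power for VAT, and both depots are equally variable, power is Φ(2.802/√(2 − 2ρ) − 1.960):

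- ρ = 0.3: 2.802/1.183 = 2.368, power 66%
- ρ = 0.5: 2.802/1.000 = 2.802, power 80%
- ρ = 0.7: 2.802/0.775 = 3.617, power 95%
- ρ = 0.85: 2.802/0.548 = 5.115, power over 99%

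**5. If SAT change is more variable.** On the cm² scale, take a differential effect of 3.57 cm², a VAT SD of 10.07 and a SAT SD twice that. The SD of the between-depot difference is 10.07 × √(1 + 4 − 4ρ), which is 19.64, 17.45 and 14.94 for ρ = 0.3, 0.5 and 0.7. With 125 per diet, power is 30%, 37% and 47%.

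**The case against.** **The 10.1 sentence does not mention SAT.** This is correct. What differs there is the effect between strategies, and the word *specifically* can be read as naming the endpoint. A reader might infer that 10.1 itself hypothesises a VAT-versus-SAT difference, but it does not. Objectives 1 and 2 also compare arms, not depots. The between-depot question rests on 2.2 and 10.2, supported by the overall aim and by the choice of fat distribution as the overall primary outcome. Section 10.2 frames it within a mediation hypothesis.

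**Nothing says that a split result will be called depot-specific.** Also correct. A reader might infer that the protocol commits to this reading, but no section does. The point is that the plan offers no other route to the claim.

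**This could be left to the SAP.** A claim rule and a named secondary contrast often are. But 10.4.1 already fixes the factors, the interaction, the covariates, the reference group and the significance level, and the resulting model does not match the hypothesis in 10.2.

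**Depots may be modelled jointly, and relative change is planned.** Both are fair. It cannot be asserted that each depot is tested in isolation, nor that the plan compares only areas in cm². A joint model could yield the contrast if someone specified it; no one has.

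**Scale.** Section 2.1 cites VAT as 18.3% of total adipose tissue in moderately obese men. A reader might infer from this how much larger SAT is in this trial. The documents do not support that: the figure is whole-body volume from a cited study, while this trial measures mean area on three abdominal slices.

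**The sizes are assumed.** They are: the correlation, the power per depot, equal standardised effects and equal variability. The ranges show that a misleading pattern is plausible; they do not predict its frequency in this trial.

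**Conclusion.** The point holds as a mismatch between hypothesis and analysis. Sections 2.2 and 10.2 ask whether the diets affect VAT differently from SAT, and 10.4.1 contains no contrast that answers this. The planned between-diet comparison of VAT is not affected by this point. Only a depot-specific, differential or preferential claim lacks a test.

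With identical standardised effects in both depots, VAT alone would be significant in about 6-13% of trials at 80% power per depot and 9-20% at 50%, for ρ between 0.3 and 0.85. An equal standardised effect is an equal proportional effect only if the log changes in the two depots are equally variable, which is a further assumption. This is worth correcting before analysis, but it does not undermine the primary endpoint.

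**What to change.** Keep VAT change as the primary endpoint. Add to 10.4.1 one prespecified secondary contrast: the between-diet (and PA) difference in 0-18-month change in log(VAT/SAT), estimated by ANCOVA with the baseline log ratio as covariate.

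State explicitly whether 18-month weight change enters this model. It is measured after randomisation and can itself be affected by diet and PA, so report the contrast without it; a weight-adjusted version can stand beside it if wanted.

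State that differential, specific or preferential depot effects will be claimed only if the 95% CI of this contrast excludes zero. Otherwise conclusions stay with each depot separately.

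The cost is a paragraph of wording and one model on areas already measured, with no added visits or scans. The downsides are one more named secondary test, a ratio scale that needs a sentence of explanation, and uncertain power. Power depends on the unknown VAT-SAT correlation and relative variability and may be well below 80%, so a CI that includes zero should not be read as showing equal effects in the two depots.
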